[figure not shown]

[figure not shown]

[figure not shown]

[figure not shown]

| **Secondary**  **Outcome**  **Measures** | 1. Patient and Carer Reported Outcomes measured at 30 days. 2. Health-related QoL (EQ-5D-3L) of patients at hospital discharge and at 30 days 3. Carer Burden Scores of carers at hospital discharge and at 30-day post-discharge 4. Measures of safety   a) Hospital device-associated infections, e.g., CAUTI, VAP, HAP, in the rate of events within the group per unit time.  b) Clinical outcomes – Bed sores, Tracheostomy block, Clinical Deterioration, readmission, and mortality (rate/ unit time).   1. Measures of process 2. Adherence to the intervention  - % consented - % Trained for at least three sessions - Number of sessions missed. - Subjective and objective scores of carers' confidence post-training - % using the mHealth app at least once spontaneously after home discharge - % 1 week home visits completed - Data entry (completion)  1. Clinical 2. Measures for Direct Analysis 3. Resource use and expenditure questionnaire |

# 2.0 SCIENTIFIC ABSTRACT

**Background** Tracheostomy, a procedure to create an opening in front of the trachea when performed on critically ill patients in intensive care units (ICUs), decreases the duration of mechanical ventilation, incidence of nosocomial infections and length of ICU stay. Its use early during (1) neuro-ICU stay is associated with improved chances of early rehabilitation and discharge due to decreased secondary insults and hospital-acquired morbidity. (1) However, when there is a lack of out-of-hospital state-sponsored or low-cost rehabilitation facilities for these chronically ill bedridden patients, timely discharge from the ICU and hospital becomes a challenge. These patients need higher intensity care at home, including care of the tracheostomy and indwelling catheters, home ventilation, nasogastric feeding, physiotherapy, and general nursing care. Fear, stigma and unpreparedness among family members and healthcare workers of caring for a patient with 'a hole in the neck' prolongs ICU and hospital stay, increasing the very morbidities the tracheostomy sought to avoid. Costs of care to the patient and family, as well as the health care system, increase as resources cannot be allocated to acutely ill patients.

To address this gap, at our centre in Eastern India, we have developed and pilot-tested the All-India Institute of Medical Sciences Intensive Care Unit (AIIMS ICU) Rehabilitation Intervention. The intervention, with its components of counselling, hands-on training, and education, facilitated discharge and post-discharge support, aims to implement family-led home rehabilitation of chronically critically ill tracheostomy patients. Adaptations were informed by a realist review of international literature on the barriers and facilitators to implementation of similar interventions and based on the MRC guidelines for evaluation of complex healthcare interventions. This paper presents a protocol for the effectiveness and process evaluation using a pragmatic design, including interrupted time series assessments in both intervention and comparison groups across three ICUs in India. (2)

**Aim**

To evaluate the AIIMS ICU Rehabilitation (AIR) intervention (effectiveness and process)

**Objectives**

- 1. To evaluate the impact of the AIR intervention on the timeliness of discharge from the hospital for chronically ill tracheostomised patients in 3 ICUs in India.
  2. To identify organisational and health system factors affecting the implementation of the intervention (process evaluation).
  3. To explore the family and healthcare provider experience of the intervention.

**Methods**

**Design Objective** 1.1 will use Interrupted time series analysis (ITS), enabling comparison over time of the population. (Workflow 1) The ITS design has been selected, given that we will have control over when the intervention is implemented in the sites. This will enable us to overcome potential challenges of between-group differences ICUs patients and providers), and potentially reduce the need to control for complex confounders (clinician behaviours, care provision/costing structures).

Objectives 1.2 and 1.3 will use mixed methods approach for the process evaluation.

**Interventions and duration.** At each site, we will compare the time to discharge of CCI tracheostomy patients, their impact on patient-family dyads, before (4 months) and after implementation of AIR (4 months). Each patient-carer dyad will be followed up after recruitment, up to one month after discharge from the hospital. Objectives 1.2 & 1.3 will proceed concurrently.

**Sample size and population.** Being an interrupted time series design, with the outcome being the mean time to discharge from the ICU/ Hospital for all eligible patients every week, there will be 16 time points before and 16 after the intervention that will provide trends of change after the intervention is implemented. To account for threats to internal validity, such as history, maturation, and instrumentation, we will employ a control group in the study. The control group will comprise non-tracheostomised patients admitted to the ICUs during the same weeks as the patients in the intervention group, the observation of interest being the mean time to discharge. There are estimated to be approximately 160 patients in the intervention arm and a similar number in the control arm. In the event that the expected number of recruitments per unit of time is inadequate, and data do not lend themselves to a stable ITS analysis, a pre-post analysis will be done, with the control arm in place.

**Primary outcome measure:** Time to discharge from ICU or hospital to home after the treating physician's assessment as 'stable' and suitable for home care.

**Secondary outcome measures:** Additional patient-reported outcomes, safety and process measures, and measures of cost to patient-carer.

**Data collection and Analysis.** Data will be collected before and after the implementation of the intervention to assess its effect. A Statistical Analysis Plan will be drawn up prior to any analysis and reviewed by the Data Safety Monitoring Committee.

**Timelines** Months 0-8: approvals and set-up; Months 8-18: process evaluation; Month 6-8: 3 units initiated; Month 8-18: all three units open (8-11 baseline data collection; 12 & 13 implementation of intervention; 14-18 post implementation data collection); Months 18-36: Patient follow up, Qualitative data collection, data cleaning, database lock, statistical cleaning, and dissemination of results.

# 3.0 LAY SUMMARY OF RESEARCH

Tracheostomy is a lifesaving procedure for patients with neurologic (brain) damage. Despite studies showing that it provides benefits such as decreased infection and time on ventilator and ICU, patients with tracheostomies and their family members (carers) suffer from a severe shortage of affordable rehabilitation facilities for these patients once they are ready to be discharged from the ICU and hospital because of various reasons: fear of caring for a patient with a 'hole -in -the neck', inadequate guidance and training of family members prior to discharge, lack of post discharge follow up. The fact is that these patients end up staying longer at hospitals, getting repeated infections leading to ICU readmissions- increasing the cost of care for patient families and leaving medical teams struggling to provide care to newer patients who need more acute attention.

The AIR intervention, however, aims to enable family-led home-based rehabilitation of these bedridden tracheostomy patients and offers patients and families something different.

i. The opportunity to discuss with counsellors and doctors about caring for their patients at home,

ii. Receive hand-held bedside training from trained nurses using modules (for tracheostomy care, indwelling catheter care, nasogastric feeding, back care, suctioning, home ventilation management and troubleshooting) that have been codeveloped by patient-family and healthcare workers, till they self-report confidence in their caring ability.

iii. Having access to free equipment for the first month of at-home rehabilitation.

iv. Facilitated discharge and follow-up for one month- ability to communicate with the rehabilitation team via a bespoke mHealth app that also acts as an education tool with a repository of videos and answers to frequently asked questions.

A preliminary study of the AIR intervention at one centre has shown that it is feasible and acceptable to patients, families, and healthcare workers. Families feel safe, confident, and happy with the AIR- many see faster recovery in their wards, and other carers can return to work faster, to begin daily earnings. However, our understanding of how much AIR can hasten discharge, decrease infections, and reduce costs for different varieties of patients in different settings is inadequate. The only way to know for sure is to compare longer periods with and without intervention in different hospitals. International trials do not faithfully explore issues that matter to bedridden tracheostomised patient- families, making it hard to assess the impact of home discharge and home care on real-life. To ensure that we capture these elements, we hope to liaise closely with all stakeholders in this study to better understand for whom, in which circumstances and how home rehabilitation intervention may or may not be effective.

In this study, the question asked is whether the AIR intervention enables timely home-discharge of bedridden tracheostomy patients, decreases complications, and reduces costs for patient-families as compared to those who do not have access to the intervention. People who are suitable and consent to take part will be divided into two groups based on having a tracheostomy. This is done to create two groups of patients, allowing for a more robust assessment of the effect of the AIR intervention. Quality of life of patients and Carer burden will be measured at discharge and on days after discharge using specially designed questionnaires. We will also collect information on OOPE of the patient-family during hospital stay and in the 1^st^ month after discharge, to understand if the AIR is cost-effective for the person and the health service. And finally, we will assess the thoughts, feedback, and live experiences of patient-carers who are enrolled in the study to identify barriers to wider implementation if we find that it benefits patient-carers and the healthcare service.

# 4.0 BACKGROUND AND RATIONALE

**4.1 Background**

The implications and outcomes (including cost) following protracted ICU stay are potentially devastating for patients who are tracheostomised and bedridden for chronic critical illness (CCI) and for their families, especially in lower-middle-income countries like India. Reasons for this include limited availability of and access to rehabilitation services, lower baseline health literacy, concomitant infections in the presence of antibiotic resistance, and spiralling financial burden associated with healthcare costs and loss of income.

For patients at risk of extended ICU stay and CCI, discharge home to be with family is a priority. Not only does timely discharge alleviate the burden of the cost of hospital care, but it may also reduce the incidence of HCAIs and provide families with opportunities to be at home with their loved ones as they attempt to recover. Structured interventions to enable family-led home rehabilitation of tracheostomised CCI patients are few and more often tailored for the paediatric population. (3) The barriers to implementation of family-led home rehabilitation of non-tracheostomised chronically ill adults are a lack of directed training, education, and support for family caregivers in the form of assistive devices and timely referral to health services. (4–8)

To meet this gap in Odisha, a state in Eastern India, a team of critical care physicians, nurses, rehabilitation specialists, and dieticians from the All-India Institute of Medical Sciences (AIIMS) designed an intervention to facilitate home rehabilitation of tracheostomised CCI patients. The endeavour was supported by the National Health Mission Odisha and Collaboration for Research, Training, and Implementation in Critical Care in Asia and Africa (CCAA)– a Wellcome Trust Innovations project.

The AIIMS ICU rehabilitation (AIR) project (Appendix 1) has designed an intervention to equip family caregivers to accept and execute home rehabilitation of chronically ill tracheostomised patients. It gives bedside education and training to carers for tracheostomy care, indwelling catheter care, nasogastric feeding, back care, suctioning, home ventilation management and troubleshooting. It has been pilot tested at a single centre and modified based on a realist review of international literature and stakeholder feedback for scale-up implementation at three centres.

This protocol describes a mixed-methods evaluation of the effectiveness and processes of the multicentric scaled-up implementation.

###### 4.2 Study Rationale

The AIIMS ICU Rehabilitation pilot project has recruited more than 200 tracheostomised chronically ill patients and their family carers for home rehabilitation. It has been pilot tested and has shown good feasibility and acceptability among stakeholders. Preliminary data show that it has reduced the length of ICU and hospital stays and frequency of hospital-acquired infections.

A realist review of international studies reporting interventions aiming to implement family-led home care of chronically ill patients indicates that interventions that include components of co-designed training, supported discharge, and home visits for post-discharge follow-up facilitate implementation and reduce the length of stay and rehospitalisation among chronically ill patients, such as stroke survivors.

# 5.0 STUDY DESIGN

###### 5.1 Controlled Interrupted time series design (work series 1)

A time series design is a continuous set of observations taken repeatedly over time. In this design, we will use a time series of our outcome of interest (time to hospital discharge) to establish an underlying trend that will be 'interrupted' by the AIR intervention at a known time. The expected trend in the absence of the intervention, or the counterfactual trend, will provide a comparator for evaluating the impact of the AIR intervention by interrogating the change in the post-intervention period. Fig. 2 illustrates the design with the graph displaying preintervention weekly trends of mean time to discharge, the counterfactual scenario (dashed line), and the hypothesised decrease in (mean) length of hospital stay every week. An appropriate ITS statistical model will be selected to provide evidence of whether the change represents a real decrease.

[figure not shown]

[figure not shown]

An ITS design is considered appropriate for our study for the following reasons-

1. An RCT is considered the gold standard for evaluating the effectiveness of interventions. However, where doing an RCT is not practical, such as in our setting, ITS design is increasingly used as it is particularly suited to interventions introduced over a clearly defined time period.
2. ITS works best with short-term outcomes expected to change quickly after an intervention is implemented. This is expected from the AIR intervention, which hopes to enable early supported discharge of patients.
3. ITS requires the availability of sequential measures of the outcome before and after the outcome, which will be possible in our study.
4. ITS is often used to evaluate natural experiments in real-world settings, thereby increasing external validity compared to RCTs.

The hypothesised impact model for our study is decided a priori based on literature and knowledge of the pilot expects a change in level without affecting the slope. If effective, the AIR intervention will follow the intervention immediately without a lag effect and decrease the average time to hospital discharge without affecting the slope (rate of discharge from the hospital), Fig. 1.

If the design of data collection within each time point does not lend itself to an ITS design, the data will be analysed using a pre-post comparison of time to discharge.

###### 5.2 Primary and secondary outcomes (TABLE 2)

**5.2.1 Primary outcome**

Time from the clinician declaring that the patient can be stepped down (Ready For Step Down) to the patient being discharged home.

**5.2.2 Secondary outcomes**

i. Patient and Carer Reported Outcomes measured at Day 30.

a. Health-related Quality of Life (QoL) with EuroQOL 3 dimensions (EQ-5D-3L) of patients at hospital discharge and at Day 30 after hospital discharge?

b. Carer Burden Scores (CBS) of carers at hospital discharge and at 30-day post-discharge

c. Alert, Verbal, Pain, Unresponsive (AVPU) scores at discharge and at 30-day

ii. Measures of safety

a. Hospital-acquired infections- central line-associated bloodstream infections, catheter-associated urinary tract infections, ventilator-associated pneumonia, surgical site infections, in the rate of events within groups per unit time.

b. Clinical outcomes – Length of stay in ICU, frequency of bed sores, tracheostomy blockage, Clinical Deterioration (as declared by the treating team in the hospital or deterioration in AVPU status at follow-up), readmission to ICU or hospital (after discharge and up to 30-day follow-up) and mortality at follow-up of 30 days (rate/ unit time).

iii. Measures of process (post-intervention stage)- Implementation Measures

1. Adherence to the intervention

- %Eligible patients approached
- % consented
- % Trained for at least 3 sessions
- Number of sessions missed.
- Subjective and objective scores of carers' confidence post-training
- % using the mHealth app at least once spontaneously after home discharge
- % 1 week home visits completed
- Data entry (completion)

| **Outcome** | **Definition** | **Assumed relationship** |
| --- | --- | --- |
| Time from the clinician's decision of readiness for step down | Time (days) from the Clinician declaring the patient ready for step down to discharge home under a carer or a paid caregiver.  *Home is defined as the usual residence, or family home, or a rental house in the vicinity of the hospital, but not another healthcare facility* | The intervention will reduce hospital length of stay/ bed days. |
| ICU/ HDU length of stay | Time from ICU admission to discharge to an intermediate facility (ie HDU/ ward) within the same hospital | The intervention will reduce ICU length of stay/ bed days. |
| Complications | Hospital-associated infections are defined as clinician-reported suspected/confirmed infection + new fever or new change in antibiotic. | There will be a reduction in HAI following the intervention. |
| 30 Day Outcomes | Mortality  Quality of Life (EQ5D)  Readmission to the same, or another healthcare facility  Caregiver Burden (by CBS scale) | There will be no worsening in patient and carer outcomes due to the intervention. |

*Table 2. Description of outcomes and assumed relationship with intervention.*

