###### *Table 2: Schedule of evaluations in the intervention group.*

**9.2 Description of Evaluations:** Detailed description in the manual of the intervention and evaluations

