| Home Visit | Care Quality: Hygiene, equipment use, trache/RT/foley care, calorie tracking, mobilisation  Support: App usage, local HCC contact, medications | ✔ | ✘ | ✘ |
| At Discharge | Dates & Status: Unit/hospital discharge date & time, CPR, discharge note  Trache-Specific: Ongoing trach care, reason for early discharge, diet chart  CG Consistency: Same carer since enrollment, eHealth tools & scores  Outcome Measures: EQ5D, VAS, CBS score, Semi-structured interview | ✔ | ✔ p | ✔ |

Table 3. Data to be collected at different time points. Tpi-Tracheostomy (post-implementation), NT=Non-Tracheostomy, C= pre implementation patients with Tracheostomy) , p=partial

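### Clinical deterioration is detected by one rule in hospital and another after discharge, so a pooled before/after rate can move with no change in true risk, in a direction the documents do not settle

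*Combined protocol and SAP*

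**What the plan says.** Section 5.2.2, under measures of safety, defines the outcome as "Clinical Deterioration (as declared by the treating team in the hospital or deterioration in AVPU status at follow-up". A team declaration counts while the patient is in hospital; a worse AVPU level counts at follow-up. The Study Summary groups it with other events as "Bed sores, Tracheostomy block, Clinical Deterioration, readmission, and mortality (rate/ unit time".

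As an outcome in its own right, AVPU appears in Section 5.2.2 as "Alert, Verbal, Pain, Unresponsive (AVPU) scores at discharge and at 30-day". The Methods in the Scientific Abstract state that "Each patient-carer dyad will be followed up after recruitment, up to one month after discharge from the hospital". For the primary outcome, the outcomes table in Section 5.2.2 expects that "The intervention will reduce hospital length of stay/ bed days".

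Two places bear on how closely patients are watched at home. The grid in Section 9.1, with contacts at days 1-3, 6-7 and 28-31 after discharge, is captioned "Schedule of evaluations in the intervention group". In Section 10, Table 3, the home-visit row ("Care Quality: Hygiene, equipment use, trache/RT/foley care, calorie tracking, mobilisation") is ticked for post-implementation tracheostomy patients and crossed for the baseline tracheostomy and non-tracheostomy groups. Table 3 has no 30-day row.

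No section applies one rule in both settings, states which patient-days form the denominator, or separates the analysis by setting.

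**The concern.** Early home discharge raises an obvious safety question: do patients deteriorate more once they leave? This outcome is the most direct measure of that, yet its ascertainment is tied to the exposure. AIR changes the patient's location, and location selects the detection rule.

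The two rules are unlikely to be equally sensitive. In hospital, a team can declare any kind of worsening on any day. AVPU is a four-level consciousness scale. It does not register infection or airway trouble in a patient who stays alert, it can miss an episode that resolves between two measurements, and it cannot fall below Unresponsive. That floor matters in a neuro-ICU tracheostomy population.

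A before/after difference in the pooled rate could therefore reflect observation alone. An apparent fall might be read as a safety benefit, or might hide harm at home. An apparent rise might be read as harm when patients were only watched more closely.

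**Working it through.** The documents give no deterioration rate, detection rate or expected stay, so there is no figure to reproduce. What follows is an illustration.

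**From the documents:** about 30 home days per patient in both phases (Methods; Section 8), and fewer hospital days after implementation (size not stated).

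**Assumed:** a constant true daily risk, the same in both settings and phases; a stay from RFSD to discharge of H = 15 days before and H = 8 days after; detection of 0.90 in hospital and h at home, with h = 0.30 and a range of 0.20 to 0.50.

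**Formula.** Recorded rate as a fraction of the true rate:

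F(H, h) = (0.90 × H + h × 30) / (H + 30)

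**Mix of time.** Hospital share before: 15/45 = 33%. After: 8/38 = 21%. Most observed time is under the home rule in both phases; the problem is that the mix shifts.

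**Equal home follow-up in both phases:**

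| h | Before | After | Ratio | Change |
|---|---|---|---|---|
| 0.20 | (13.5 + 6)/45 = 0.433 | (7.2 + 6)/38 = 0.347 | 0.80 | -20% |
| 0.30 | (13.5 + 9)/45 = 0.500 | (7.2 + 9)/38 = 0.426 | 0.85 | -15% |
| 0.50 | (13.5 + 15)/45 = 0.633 | (7.2 + 15)/38 = 0.584 | 0.92 | -8% |

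**Other stays.** Let s be home detection relative to hospital detection; the after/before ratio then uses (H + 30s)/(H + 30). For stays of 20 then 10 days the ratio is 0.71 (s = 0.1), 0.80 (0.25), 0.89 (0.5), 0.96 (0.75), 1.00 (1.0) and 1.03 (1.2). With equal follow-up, the recorded rate falls only if home detection is below hospital detection.

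**Unequal home follow-up.** Keep h = 0.30 before and find the value after implementation at which the artefact disappears:

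(7.2 + 30h)/38 = 0.500, so h = (19.0 - 7.2)/30 = 0.393

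Above about 39% the recorded rate rises. At h = 0.50 after against 0.30 before, the ratio is 0.584/0.500 = 1.17, a spurious increase of 17%. For stays of 20 then 10 days, the break-even relative detection after implementation is 0.20, 0.40 or 0.60 when the baseline value is 0, 0.25 or 0.5.

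**The case against.** **Direction.** A reader might infer that sending patients home must lower the recorded rate, so that the error favours AIR. The documents do not support that. It requires home detection to be lower than in hospital and equal in the two phases. The first is likely but unquantified; the second is doubtful. The post-discharge grid is captioned for the intervention group, and the home-visit row is crossed for baseline patients. Closer contact after implementation pushes the recorded rate up. This objection stands and limits the point to an artefact of unsettled direction. It does not rescue the pooled rate.

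**Missed events.** A reader might also infer that a transient episode at home leaves no trace. That goes too far. Tracheostomy blockage is a separate outcome, and so are "readmission to ICU or hospital (after discharge and up to 30-day follow-up) and mortality at follow-up of 30 days (rate/ unit time"; the Section 9.1 grid also carries infections and adverse events. The definition's reference to follow-up is not tied to day 30 either: only the separate AVPU outcome names that day, and other contacts might record AVPU. The documents do not say that they do. Severe events are thus partly caught elsewhere, but the deterioration outcome itself stays uneven.

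**Pooling.** In Section 5.2.2 the per-unit-time note ends a list that includes ICU length of stay, so it cannot govern every item there. That is fair. The Study Summary list has no length of stay, however, and there the note naturally covers deterioration. A single rate is the plain reading, though not an explicit instruction.

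**Importance.** This is one of several secondary safety items. It is absent from the outcomes table in Section 5.2.2, whose expectation of no worsening rests on mortality, quality of life, readmission and caregiver burden. The primary outcome is unaffected. This stands and limits the severity.

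**Conclusion.** The point holds in a limited form. The outcome has two detection rules selected by location, AIR is intended to change location, and nothing in the plan separates the two. A pooled before/after rate can therefore change while true risk does not.

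Under equal home follow-up and poorer detection at home, the illustration gives a spurious fall of about 15%, with a range of 8% to 20%. It rests on assumed stays, assumed detection rates and a constant daily risk. Under closer home contact after implementation, the same example crosses zero at about 39% home detection and then shows a spurious rise. The documents do not allow a choice between these, so neither a bias in favour of AIR nor one against it can be asserted. What can be said is that the pooled rate would not be interpretable as evidence on safety. The change should be made, but it does not bear on the primary analysis.

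**What to change.** Do not pool the two rules. Report two separate outcomes:

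1. Team-declared deterioration in hospital, counted from RFSD, per in-hospital patient-day.
2. Change in AVPU from discharge to day 30, among survivors assessed at day 30 who were not already Unresponsive at discharge. State the numbers excluded, and read the result beside mortality, since the denominator is conditional on survival.

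For the before/after comparison, use only post-discharge assessment times that apply in both phases. State in Section 9.1 and Table 3 which contacts baseline patients receive. Findings from additional contacts after implementation can be described but should not enter the comparison.

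Rest the safety comparison across settings on the 30-day mortality and readmission outcomes already listed. A new composite would not solve the problem: return from ward to ICU before discharge is not a listed outcome, and hospital readmission can occur only after discharge, so a composite counted from RFSD would again depend on location.

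The cost is wording in the outcome definitions and analysis plan. For data already collected, splitting by setting is an analysis change; if baseline patients had no day-30 AVPU score, the second outcome can only be descriptive for the post-implementation phase. The downside is small: there is no single overall deterioration rate.

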**Semi- structured interviews**

3. Semi-structured interviews with patient–carer dyads conducted approximately one month after recruitment (recruitment is at the time of RFSD), including 3a. Carers who received the intervention and

3b. baseline-period participants describing their lived experience of home discharge without the intervention;

3c. Semi-structured interviews with ICU nursing staff and Site PIs exploring perceptions of usual care, experiences of the intervention, and expectations for future home discharge will be undertaken after completion of the study

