# 8.0 DURATION OF ENROLLMENT AND FOLLOW-UP

The trial will begin pre-intervention data collection for tracheostomised patients for 4 months before implementation of the intervention (over 30 days). After the implementation, data will be collected for 4 months. The individual participant will be enrolled in the ICU and followed up after home discharge for 30 days.

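### The 30-day safety outcomes run from discharge, which AIR is designed to bring forward, and the infection rate has no stated denominator, so the two periods are not compared like for like

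*Combined protocol and SAP*

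**What the plan says.** Readmission has an explicit origin at discharge: "readmission to ICU or hospital (after discharge and up to 30-day follow-up"). Mortality is given as "mortality at follow-up of 30 days (rate/ unit time"), with no origin in that sentence. Section 8.0 says participants are "followed up after home discharge for 30 days", and the last dated visit in the section 9.1 schedule is at days 28 to 31 after discharge, so discharge is the natural reading for mortality too. The Methods part of the abstract describes a longer observation period: "Each patient-carer dyad will be followed up after recruitment, up to one month after discharge from the hospital".

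Infections are to be expressed "in the rate of events within groups per unit time". Neither section 1.0 nor section 5.2.2 says whether the unit is patient-days, device-days or calendar weeks.

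The outcomes table in section 5.2.2 expects shorter stay and fewer hospital-associated infections. For the 30-day outcomes it states: "There will be no worsening in patient and carer outcomes due to the intervention". Section 4.1 links fewer infections to timely discharge.

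RFSD starts the primary outcome (section 5.2.1), and section 5.3.1 notes that "recruitment is at the time of RFSD". No safety outcome is tied to it.

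**The concern.** The start of the safety window is itself a result of the intervention. If AIR works, patients after implementation enter their 30 days sooner after RFSD than baseline patients did. Where risk falls as time since RFSD passes, the later period is then observed over a riskier stretch, while baseline deaths on the same days after RFSD fall before discharge and outside the window.

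Infections raise a related problem. The expected benefit works largely by removing hospital days. A rate per hospital day divides by the very quantity that AIR reduces, so that part of the benefit does not appear.

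These are secondary outcomes, but they carry the argument that sending tracheostomised patients home earlier is safe. No margin or test accompanies the expectation of no worsening, so readers will judge it mainly from point estimates, and a window artefact moves those directly.

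**Working it through.** **Inputs from the documents.** Section 1.0 gives about 5 discharges at each of 16 + 16 weekly points: 32 × 5 = 160, which matches the stated 160 tracheostomy patients, or about 80 per period. This is a count, not a power calculation. The documents give no baseline stay, mortality, infection rate, margin or power. All such values below are assumptions, shown over a range.

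**Mortality.** Use one hazard from RFSD, identical in both periods, so the true effect is zero. Take cumulative hazard H(t) = −ln(1 − p) × (t/60)^k, with p the 60-day mortality (20% or 30%), k = 1 constant and k = 0.7 or 0.5 falling. Let L be days from RFSD to discharge.

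- Reading A, 30 days from discharge: 1 − exp(−[H(L+30) − H(L)])
- Reading B, RFSD to discharge plus 30: 1 − exp(−H(L+30))
- Fixed horizon, RFSD to day 30: 1 − exp(−H(30))

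Results for p = 20%:

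| k | L, before → after | Reading A | Ratio A | Reading B | Ratio B | Fixed, both periods |
|---|---|---|---|---|---|---|
| 1.0 | 14 → 7 | 10.6% → 10.6% | 1.00 | 15.1% → 12.9% | 0.85 | 10.6% |
| 1.0 | 28 → 7 | 10.6% → 10.6% | 1.00 | 19.4% → 12.9% | 0.66 | 10.6% |
| 0.7 | 14 → 7 | 9.4% → 10.4% | 1.10 | 16.4% → 14.7% | 0.89 | 12.8% |
| 0.7 | 28 → 7 | 8.3% → 10.4% | 1.24 | 19.6% → 14.7% | 0.75 | 12.8% |
| 0.5 | 14 → 7 | 8.0% → 9.4% | 1.18 | 17.4% → 16.1% | 0.92 | 14.6% |
| 0.5 | 28 → 7 | 6.5% → 9.4% | 1.46 | 19.7% → 16.1% | 0.82 | 14.6% |

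Over the whole grid (also 10 → 5 and 21 → 7 days, and p = 30%), ratio A is 1.08 to 1.46 for falling hazards and 1.00 for a constant hazard. Ratio B is 0.66 to 0.94. Dividing by person-time does not cure reading A: for falling hazards those rate ratios are 1.09 to 1.49. Only the fixed horizon returns 1.00 in every case.

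A step hazard shows the mechanism by hand: 1% per day to day 14 after RFSD, then 0.3% per day.

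- Discharge at day 20: 1 − exp(−0.003 × 30) = 8.6%
- Discharge at day 8: 1 − exp(−(0.01 × 6 + 0.003 × 24)) = 12.4%, ratio 1.44
- RFSD to day 30, either way: 1 − exp(−(0.01 × 14 + 0.003 × 16)) = 17.1%

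This example is steep: it implies 1 − exp(−0.14) = 13% mortality in the first 14 days.

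With 80 per period, the chance of a statistically significant false harm result under reading A is about 4% to 14% for falling hazards, against 2.5% nominal.

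**Infections.** Expected infections per patient = daily rate × hospital days.

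| Assumption, stay after RFSD 14 → 7 days | Per 100 patients | Per 1000 patient-days | Per week at 5 patients |
|---|---|---|---|
| 15 per 1000 days, from RFSD only | 21.0 → 10.5 (−50%) | 15.0 → 15.0 (ratio 1.00) | 1.05 → 0.53 |
| Plus 20 earlier days; 20 per 1000 before RFSD, 10 after | 54.0 → 47.0 (−13%) | 15.9 → 17.4 (ratio 1.10) | 2.70 → 2.35 |

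In the second row, 0.40 + 0.14 = 0.54 infections over 34 days becomes 0.40 + 0.07 = 0.47 over 27 days. The rate rises because the days removed are the lower-risk ones.

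**The case against.** A reader might infer that the plan is biased against AIR. The documents do not support a direction. The mortality origin is inferred from the follow-up text and the schedule, and nowhere is it said that in-hospital deaths after RFSD are left out. Following dyads from recruitment could mean they are counted, and reading B then favours AIR. Reading A also gives no artefact under constant hazard and often a modest one, and eligibility requires that patients be expected to survive. On the other hand, section 6.2 does not exclude short life expectancy after discharge, so falling risk is plausible, though unsourced.

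A reader might also infer that the infection benefit must disappear. That needs a denominator of patient-days or device-days. The study's analytic unit is the week, and per week the reduction remains. A rate per exposure day also answers a legitimate question, and rate and stay reported together allow burden per patient to be recovered. What stands is that the unit is undefined and the choice changes the answer.

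Finally, a reader might conclude from "Schedule of evaluations in the intervention group" and from Table 3 that baseline 30-day events are not ascertained. Table 3 is indicative and has no 30-day row for any group, its home-visit row records care quality and support, and the text promises one-month follow-up to every dyad. What stands is narrower: Table 3 crosses the post-ICU row for baseline tracheostomy patients, which puts their in-hospital data after ICU in doubt.

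The outcomes table states expected relationships, not hypothesis tests, so it would be wrong to say that a formal safety test is invalid.

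**Conclusion.** The point holds as a matter of comparability, not of a known direction of bias. Readmission is explicitly, and mortality probably, counted from a time that the intervention moves, although RFSD is available as a common start. Under assumed falling hazards, equal mortality gives a ratio of about 1.1 to 1.5 from discharge; under all assumed hazards it gives 0.66 to 0.94 from RFSD to discharge plus 30. The effect is mainly on point estimates, and a significant false harm result is uncommon. The infection rate can show no change while infections per patient halve, but only with an exposure-day denominator. The sizes rest on assumed hazards, stays and infection rates. The remedy also assumes that RFSD is declared at a comparable stage of recovery in both periods, as the primary outcome already does.

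**What to change.** In the SAP:

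1. Make the between-period mortality comparison from RFSD to day 30 in all enrolled tracheostomy patients, including in-hospital deaths and patients never discharged home.
2. Add days alive and at home from RFSD to day 30, so that readmission is covered on the same clock.
3. Report infections per patient from RFSD beside the exposure-time rate, and state the denominator of that rate.
4. Keep the 30-day post-discharge figures as supporting results.

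Before committing, confirm that RFSD date, in-hospital infections after ICU and 30-day status were captured for baseline tracheostomy patients. Where they were not, limit the comparison to mortality, or to infections in the ICU days collected in both periods, and say so in the report.

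The cost is a few SAP definitions and a little more analysis. Discharge cannot precede RFSD, so for patients discharged home the planned follow-up already reaches RFSD plus 30 days. For patients never discharged home, day-30 status must be checked separately, because section 8.0 ties follow-up to home discharge. The main downside is that the per-patient infection comparison may not be possible for the baseline period.
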